Along with the previously mentioned factors, socio-economic status (SES) has also been identified as a determinant for later obesity (11). Indeed, children with lower SES families have a steeper weight gain trajectory from birth with higher risk of obesity in adulthood (12, 21). Furthermore, children in poverty are more likely to become adults with lower SES and less wealth to pass on to future generations, in a vicious cycle, clearly acknowledging that obesity is increasingly related to poverty and is likely to be passed onto subsequent generations (22). Moreover, factors related to the socio-spatial environment play a key role in obesity (16, 23–25). For instance, the lack of healthy food availability, affordability and accessibility (e.g., food desert) has been positively linked to obesity. High neighbourhood walkability has been found to be associated with decreased prevalence of overweight and obesity, as well as the proximity to recreational facilities, parks, playgrounds, etc. have all been reported to be facilitators of physical activity (22, 26).

The overall aim of the FACILITY (feeding the aamily—the intergenerational approach to fight obesity) project is to identify determinants for early onset of childhood obesity considering both maternal and children risk factors in a sample of mother-child dyads attending a paediatric outpatient clinic of the Buzzi Children's Hospital in Milan, Italy. More in detail, the cross-sectional study aims at (i) estimating the prevalence of overweight and obesity in the target population, thus, providing updated estimates in the Milan area, a useful data for the planning of public health interventions; (ii) assessing the impacts of lifestyle and of socio-economic-cultural and environmental factors on overweight and obesity (Figure 1).

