#### Anthropometric variables

Anthropometric measures of mothers will be collected using standardised procedures (27–29), weight (kg) will be measured with a calibrated weighing scale wearing underpants only (accuracy ± 100 g), height (cm) by a fixed stadiometer with a vertical backboard and a moveable headboard (accuracy ± 1 mm) and waist circumference (cm) will be measured with an elastic tape.

Height (cm) and weight (kg) will be collected also for children/adolescents. Briefly, standing height will be measured as previously described and according to standard procedures (28, 29). Recumbent length will be assessed for children who still are unable to stand up (29). Body weight of unclothed children/adolescents will be collected using a balanced weight scale (accuracy ± 100 g), following standardised procedures (29). WHO child growth standards will be used to diagnose overweight (BMI Z-score >1) or obesity (BMI Z-score ≥2) (50). Infant growth curves from the paediatric booklet will be requested to evaluate the time (year) of the adiposity rebound. The presence of an early adiposity rebound (EAR) will be identified when the lowest BMI during child growth occurs at an age <5 years old (30, 31) and children/adolescents will be categorised into early or non-early adiposity rebound (AR). Waist circumference (cm) will be collected in children/adolescents using standardised procedures (29).

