### Data analysis

2.4

In the cross-sectional study, sample size has been determined considering a prevalence of overweight and obesity in the target population of 17% and 4%, respectively (55). Considering a 95% level of confidence and 5% precision, 217 individuals for overweight and 52 for obesity prevalence estimates are required, for a total sample size of 269 mother-child dyads.

Enrolled subjects will be described with reference to all the collected variables by means of standard descriptive statistics. Prevalence of overweight and obesity will be estimated along with 95% confidence intervals. In order to assess the impacts of lifestyle and socio-economic, cultural, and environmental factors on overweight and obesity, logistic regression will be adopted. Overweight and obesity in children, as binary variables, will be the response in two separate logistic models, where socio-economic, cultural, and environmental factors, among all collected data, will be the independent variables. Indeed, performing different analyses according to the BMI status (overweight/obesity) will capture different health correlations, since the greater severity of overweight and obesity usually corresponds to an unhealthy lifestyle, and to a low SES (12, 21). Analyses will also be adjusted for potential confounders like age, sex or any other variable identifiable as such among the collected data.

Furthermore, if sample size allows, subgroups analysis by ethnicity (Caucasian or non-Caucasian) will be performed since it likely results in different cultural habits, impacting nutrition and other lifestyle factors (56, 57).

Missing data will be handled with multiple imputation.

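### Aim (ii) is analysed only through two yes/no cuts of a measured BMI Z-score; a pre-specified companion analysis of the Z-score itself should stand beside the logistic models

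*Protocol article*

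**What the plan says.** Aim (ii) in the Introduction is "assessing the impacts of lifestyle and of socio-economic-cultural and environmental factors on overweight and obesity". Section 2.4 (Data analysis) names the method: "In order to assess the impacts of lifestyle and socio-economic, cultural, and environmental factors on overweight and obesity, logistic regression will be adopted". It then fixes the response: "Overweight and obesity in children, as binary variables, will be the response in two separate logistic models". The reason given for two models is that associations are expected to differ with the severity of excess weight.

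Under Anthropometric variables in section 2.2, "Height (cm) and weight (kg) will be collected also for children/adolescents", and the two outcomes are defined as cuts of one score: "WHO child growth standards will be used to diagnose overweight (BMI Z-score >1) or obesity (BMI Z-score ≥2". The score is therefore available on its full scale for every child with valid measurements. Section 2.4 names no continuous or ordinal analysis of it.

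The sample size in section 2.4 is set by precision of two prevalence estimates, "considering a prevalence of overweight and obesity in the target population of 17% and 4%, respectively". No effect size or power is given for aim (ii).

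**The concern.** Cutting a measured score at a high threshold discards every difference among the children on the same side of the cut. At the planning prevalences, most children fall in the zero class of both models. The WHO cut-offs are cited for diagnosis, which serves the prevalence estimates of aim (i) directly. The reason given for two models explains why severity is examined, but not why the score itself is left out. Because the sample size was not chosen for aim (ii), nothing in the design makes up for the lost information, and the study examines many lifestyle, socio-economic, cultural and environmental factors. A moderate factor that moves the whole BMI distribution could be missed in both logistic models although the data already collected could show it.

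**Working it through.** **1. The plan's own figure.** Section 2.4 states: "Considering a 95% level of confidence and 5% precision, 217 individuals for overweight and 52 for obesity prevalence estimates are required". With n = 1.96² p(1−p)/0.05², p = 0.17 gives 216.8, so 217 reproduces. For p = 0.04 the result is 59.0, so 52 does not reproduce; that is a separate matter and does not affect this point. The stated total of 269 is used below.

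**2. Expected cases.** 269 × 0.17 = 45.7 overweight; 269 × 0.04 = 10.8 obese.

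**3. Assumptions (not in the documents).** A binary factor is held by a share f of children and shifts a normal Z-score by d SD. The test is two-sided at 5%, and the 269 children are treated as independent.

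**4. Linear model of the score.** Power = Φ(d√(N f(1−f)) − 1.96). For d = 0.35 and f = 0.5: 0.35 × √67.25 = 2.870, and Φ(0.910) = 82%.

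**5. The same shift seen through the overweight cut.** With an overall prevalence of 17%, the shift gives 21.4% overweight among exposed and 12.6% among unexposed children: a difference of 0.0873, odds ratio about 1.88. The standard errors are 0.0458 (null) and 0.0455 (alternative). Power = Φ((0.0873 − 1.96 × 0.0458)/0.0455) = 48%.

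**6. Range for the overweight cut at 17%.**

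| Exposed | Shift (SD) | Linear | Overweight cut | Gap (points) |
|---|---|---|---|---|
| 50% | 0.20 | 38% | 19% | 18 |
| 50% | 0.30 | 69% | 37% | 32 |
| 50% | 0.35 | 82% | 48% | 34 |
| 50% | 0.40 | 91% | 58% | 32 |
| 50% | 0.50 | 98% | 77% | 22 |
| 30% | 0.20 | 32% | 19% | 13 |
| 30% | 0.30 | 62% | 37% | 25 |
| 30% | 0.35 | 75% | 47% | 28 |
| 30% | 0.40 | 85% | 57% | 28 |
| 20% | 0.20 | 26% | 17% | 9 |

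Simulation at 0.20 SD with 15–30% exposed gives a gap of about 5–12 points.

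**7. Simulation check.** 2,000 studies per scenario were simulated, with age and sex in the models and HC3 standard errors for the linear model. The score was calibrated to the planning prevalences, with overweight either including obesity or not. For shifts of 0.30–0.40 SD and 30% or 50% exposed, the gap was about 22–34 points. If the overweight response excludes obese children, its power falls to about 30% at 0.35 SD and 50% exposed. With the Introduction's Italian figure of 29.8% for overweight and obesity together, the formula of step 5 gives a gap of about 20–24 points for the same shifts and exposures.

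**8. Obesity model.** At d = 0.35 and f = 0.5 the normal approximation gives 23% power, and simulation with a likelihood-ratio test gives about 25–27%. A Wald test gives about 14%, but with some 11 events that test behaves badly, so 14% overstates the loss.

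**9. Information retained.** For small shifts, the efficiency of a cut relative to the full score is φ(c)²/[p(1−p)]. At 17%: 0.2531²/0.1411 = 0.45, worth about 122 of 269 children. At 4%: 0.0862²/0.0384 = 0.19, worth about 52.

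**10. A different kind of effect.** Suppose the factor adds 0.8 Z only in children already above Z = 0.3 (also an assumption). Simulated power is then 22–40% for the linear model and 89–97% for the overweight model. If the factor multiplies the SD by 1.4 without moving the mean, the linear model has 4%, the overweight model 31–33% and the obesity model 47–50%. The order reverses in both cases.

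**The case against.** The strongest reply is that the logistic models answer the question asked. Aim (ii) is worded in terms of overweight and obesity, both are defined by cited WHO cut-offs rather than chosen from the data, and a mean Z-score difference is another estimand: it counts a move from −2 to −1 like a move from 1 to 2. Section 2.4 also expects associations to vary with severity, which a single linear effect cannot show, and step 10 shows that the linear model can then be much the weaker one. All of this stands. A reader might infer that the binary models are an error, or that the Z-score should become the main response. The documents support neither.

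The power gap also depends on assumptions, because the documents give no effect size or exposure share. A loss of 20–35 points is not a general property of this plan.

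A reader might further infer that non-significant results will be reported as absence of impact. No section sets such a rule, and the Discussion calls the first analysis exploratory.

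Finally, the article is condensed, and a supporting continuous model may stand in an analysis plan that is not shown. The point therefore rests on what section 2.4 positively fixes: the response scale and the model.

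**Conclusion.** The concern holds as a case for adding an analysis. It does not show that the planned models are wrong. Using only two cuts of a measured score loses substantial information when a factor shifts the whole distribution: roughly 20–35 points of power against the overweight model for shifts of 0.30–0.40 SD, with 30–50% exposed, a normal score and the stated prevalences. The loss against the obesity model is larger, at about 82% versus 25–27% for 0.35 SD and 50% exposed. Against the overweight model, the gain shrinks to about 5–20 points at 0.20 SD and becomes a loss when the effect sits mainly in the upper tail. Neither scale is better for every plausible pattern, so both should be reported. Whether the Z-score should be ranked above the logistic models is a trade-off on which reasonable statisticians would differ; adding it beside them is not.

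**What to change.** Keep the two logistic models for aim (ii) and the WHO cut-offs for the prevalence estimates of aim (i). Add to section 2.4 a pre-specified companion analysis: linear regression of the continuous BMI Z-score with robust standard errors, using the same independent variables and confounders, reported as a mean difference with 95% confidence interval beside the odds ratios.

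The cost is one sentence in the plan and one extra model per set of factors, with no new data or participants. The drawbacks are that a mean difference is less directly clinical than an odds ratio and is insensitive to effects confined to the tail, which is why it should accompany the logistic results and not replace them.

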## Introduction

1

The Global Strategy for Women's, Children's, and Adolescents' Health (2016–2030) (1) plays a central role in the objective 3, Health and Well-being of the Agenda for Sustainable Development (2) for a future world in which every woman, child, and adolescent realises their rights to physical and mental health and well-being, in every setting (3). Obesity is defined as abnormal or excessive fat accumulation that poses a risk to health, due to an energy imbalance between energy intake and energy expenditure (4, 5). The reasons for this imbalance are complex and multifactorial (6). Health and nutritional status, lifestyle habits, biological features, environmental and socio-economic factors are nested within the family context, which in turn is nested within the community and the wider socio-geographical and cultural background (7).

Paediatric obesity has been described by the World Health Organization (WHO) as one of the most serious public health challenges of the 21st century (8). Over the past four decades, the number of children and adolescents with obesity has increased between 10 and 12-fold worldwide (9–11), with a rising prevalence among socially disadvantaged groups from low socio-economic backgrounds (11–13). In Italy, the prevalence of overweight and obesity for children aged 6–9 years is 29.8%, with the percentage of overweight and obesity around 20.4% and 9.4%, respectively (4).

Obesity prevention is recognized as the most feasible option for curbing the paediatric obesity epidemic (14). Most childhood obesity prevention programs have focused on school-aged children and have not proven so far to be effective in reversing the rising rates of childhood obesity (7). Indeed, by primary school entry, about 1 in 5 school-aged children were affected by obesity (15), suggesting that a prime opportunity to prevent childhood obesity has been missed (7). Thus, the prevention program should start very early, during and even before pregnancy and be shaped on mother-child dyads (16).

Maternal health is critical for healthy child growth and development (17). Indeed, maternal factors [i.e., Body Mass Index (BMI)], combined with an unhealthy family background (i.e., unhealthy eating habits and sedentary behaviour), strongly determine the lifestyle and nutrition behaviour of the child, predisposing him/her to the development of overweight or obesity (7, 18–20).

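### Overweight (Z>1) has no upper bound and overlaps obesity (Z≥2), so two separate binary models do not isolate the severity difference they are meant to show

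*Protocol article*

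**What the plan says.** Three places in the protocol article bear on this.

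- **Section 2.2, Anthropometric variables**, sets the cut-offs: "WHO child growth standards will be used to diagnose overweight (BMI Z-score >1) or obesity (BMI Z-score ≥2". Overweight has a lower limit only.
- **Section 2.4, Data analysis**, sets the models: "Overweight and obesity in children, as binary variables, will be the response in two separate logistic models". No child is excluded from either model and no reference group is named. The reason given for two models is that "performing different analyses according to the BMI status (overweight/obesity) will capture different health correlations", which the article ties to the severity of the excess weight. The planning prevalences come from the same section: "considering a prevalence of overweight and obesity in the target population of 17% and 4%, respectively".
- **Section 1, Introduction**, uses the two labels for national figures that add up: "29.8%, with the percentage of overweight and obesity around 20.4% and 9.4%, respectively".

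Nowhere does the article say whether a child counted as obese is also counted as overweight.

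**The concern.** Read literally, a child with Z = 2.5 meets both definitions. The Introduction uses the same two words for classes that do not overlap. The coding of the overweight outcome is therefore open, and it affects both aims of the study.

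For the prevalence aim, the reported overweight figure has two possible values, which differ by the whole obesity prevalence.

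For the regression aim, the cases and the reference of each model depend on the reading. A binary obesity outcome over all children puts the overweight among the non-cases. The two sets of odds ratios then rest on different or overlapping groups. A difference between them, or the lack of one, need not reflect severity, which is the reason given for fitting two models.

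**Working it through.** **Inputs from the article.** Cut-offs Z>1 and Z≥2 (section 2.2); two binary models, prevalences 17% and 4%, N = 269 (section 2.4); national 29.8%, 20.4% and 9.4% (section 1).

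**Assumptions, not from the article.** A binary exposure present in 40% of children with Z≤1; true odds ratios against Z≤1 of 2 for 1<Z<2 and 4 for Z≥2. Each model is taken as cases against all other children, the natural reading of a binary response over the whole sample.

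**Step 1: the prevalence label.** The national figures reproduce as exclusive classes: 20.4 + 9.4 = 29.8. Under the Z>1 definition, overweight on those figures would be 29.8%, not 20.4%. For the planning figures:

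- if the 17% excludes obesity, overweight is 17% (exclusive) or 17 + 4 = 21% (Z>1);
- if the 17% includes obesity, it is 17 − 4 = 13% (exclusive) or 17% (Z>1).

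**Step 2: who sits in which group at N = 269.**

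| | 17% excludes the 4% | 17% includes the 4% |
|---|---|---|
| Z≤1 | 79%, 212.5 | 83%, 223.3 |
| 1<Z<2 | 17%, 45.7 | 13%, 35.0 |
| Z≥2 | 4%, 10.8 | 4%, 10.8 |
| Overweight share of the obesity model's non-cases | 0.17/0.96 = 17.7% | 0.13/0.96 = 13.5% |
| Obese share of the overweight model's non-cases, coded 1<Z<2 | 0.04/0.83 = 4.8% | 0.04/0.87 = 4.6% |
| The same, coded Z>1 | 0 | 0 |

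**Step 3: odds ratios when severity matters (true 2 and 4).** Exposure odds are 0.4/0.6 = 0.667 for Z≤1, 1.333 for 1<Z<2 (57.1% exposed) and 2.667 for Z≥2 (72.7% exposed). With classes of 79/17/4%:

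- *Overweight coded 1<Z<2.* Reference exposure (0.79×0.400 + 0.04×0.727)/0.83 = 0.416, odds 0.712. OR = 1.333/0.712 = 1.87.
- *Overweight coded Z>1.* Case exposure (0.17×0.571 + 0.04×0.727)/0.21 = 0.601, odds 1.507. OR = 1.507/0.667 = 2.26.
- *Obesity.* Reference exposure (0.79×0.400 + 0.17×0.571)/0.96 = 0.430, odds 0.755. OR = 2.667/0.755 = 3.53.

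With 83/13/4% the same steps give 1.88, 2.33 and 3.63. With the national 70.2/20.4/9.4% they give 1.71, 2.45 and 3.41.

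**Step 4: odds ratios when severity does not matter (true 2 and 2).** Both excess-weight classes are then 57.1% exposed. Overweight coded Z>1 gives 2.00. Coded 1<Z<2, it gives 1.93 (79/17/4%). Obesity gives 1.333/0.755 = 1.76, or 1.82 with 83/13/4%. With 30% exposure instead of 40%, obesity gives 1.75 and 1.81. The models differ although the two classes relate to the exposure identically, and the obesity odds ratio is the smaller one.

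**The case against.** The strongest reply has four parts.

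**The literal definition gives a clean overweight model.** A reader might infer that neither model compares with children free of excess weight. The documents do not support that. If overweight means Z>1, its non-cases are Z≤1, with no overweight or obese child among them. Obese children enter the overweight reference only if the classes are exclusive, and then they do not overlap. This part of the reply stands.

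**The two models are not beyond comparison.** Under the literal definition, Z>1 and Z≥2 are the two cumulative splits of an ordered outcome and could be contrasted if fitted jointly. The article also promises no formal test of a difference between odds ratios. That stands too: the point is only that two separate fits do not supply the contrast.

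**Reference coding is detail for a fuller document, and obese against not obese is a legitimate question.** Silence on the reference group is indeed no fault in a condensed article, and 3.53 is a correct answer to that question. What remains is that the article itself states cut-offs, binary outcomes and a severity rationale that do not fit together well. The national figures are background and do not define this study's outcome. They show only that the article uses the same labels in another sense.

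**The shifts are small beside the sampling error.** About 11 obese children are expected. Split 8 exposed to 3 unexposed, the standard error of the log odds ratio is at least √(1/8 + 1/3) ≈ 0.68, a 95% factor of about 3.8 either way. Moving from 4.0 to 3.53 is 0.125 on the log scale, under 0.2 standard errors. This stands, and it limits the weight of the point.

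**Conclusion.** The point holds in a limited form. The overweight class has no upper bound, and the article does not say whether overweight includes obesity. As plain binaries, the obesity model has overweight children among its non-cases on either reading, and the overweight model changes its cases or its reference with the reading. A true overweight odds ratio of 2.0 would appear as 1.87 or 2.26, and an obesity odds ratio of 4.0 as 3.53, at 79/17/4%. Equal true odds ratios of 2 would appear as 2.00 or 1.93 against 1.76.

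These sizes rest on the assumed exposure and odds ratios, and on coding each outcome against all other children. Whether the 17% includes the 4% cannot be settled from the article, so both compositions are shown. The uncertainty in the overweight label does not depend on the odds-ratio assumptions: 4 percentage points on the planning figures and 9.4 on the national ones, against a planned precision of 5.

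This is a worthwhile improvement to the definition and the analysis, not a must-fix error.

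**What to change.** - Define three exclusive classes: Z≤1, 1<Z<2 and Z≥2. Report the prevalence of each, and of excess weight (Z>1) under its own name.
- Replace the two binary models by one multinomial logistic model with Z≤1 as reference. It gives both odds ratios against the same children and allows them to be compared directly. State that Z≤1 includes any underweight children.
- If two binary models are kept, set each excess-weight class against Z≤1 and leave the other class out.
- Do not use a proportional-odds model to show differences by severity, because it forces one common odds ratio across the cut-points.

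The change needs no new data, only wording settled before analysis. The cost lies in sparse obesity estimates: about 11 children at the assumed 4% of 269, so that contrast supports few covariates however the outcome is coded. The two-model option also leaves about 35 to 46 overweight children out of the obesity model, and about 11 obese children out of the overweight model.
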